## **3.2 Adherence and protocol deviations**

The number of days with activity in the MSDeprexis programm by each patient is assessed as a measure of treatment adherence.

## **3.3 Analysis populations**

### **Full analysis set (FAS)**

The FAS is based on the intention-to-treat (ITT) principles. This means that all randomized patients with at least one post-baseline assessment will be included in the analysis. A modified ITT (mITT) population will be analysed in a sensitivity analysis. It includes those patients who have registered in the program MSDeprexis.

### **Safety Set (SS)**

All subjects who have registered in the program MSDeprexis will be included. Subjects will be analysed according to the treatment they received.

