## 1 Introduction

This document has been written based on information contained in the trial protocol version 1.1, 02/2017. It describes the analysis after the first 12 weeks. The analysis after 12 months will be listed in a second Statistical Analysis Plan (SAP).

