## 2 Study methods

### 2.1 Trial design

IDEMS is a three arm, randomized, controlled, international multicentre trial with five academic centres. Patients are randomized to one of the three treatment groups after informed consent. One group uses only MSDeprexis for 12 weeks, the other group uses MSDeprexis with an added email support for 12 weeks and the third group is a waitlist control group.

The potential of a booster session to enhance maintenance is analysed in patients who were randomized to either the MSDeprexis or the MSDeprexisPlus group. These patients will be re-randomized to receive additional booster session (see Figure 1). This analysis is not part of this SAP.

[figure not shown]

Figure 1: Trial Design Schematic and Treatment Plan.

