### **5.4 Harms**

Adverse events will be summarized as frequencies and percentages by intervention group. New occurrence of suicidal ideation or intent as well as worsening of depressive symptoms above the clinical threshold are considered as potential adverse events. Every AE fulfilling one of the following criteria is a SAE:

- Suicidal ideation or intent (as measured by a score of 3 on BDI-II item 9 at any assessment, during the clinical interview at V2 or spontaneous report in a web message to the therapist or by contacting the study site)
- Hospitalization due to psychiatric disorder classified according to ICD10 or DSM5
- Lethal or life-threatening (incl. suicide or suicide attempt).

However, the intervention is generally considered low risk as Deprexis has been used in numerous clinical trials without evidence for adverse events and is categorized as a “low risk” medical device according to its German CE®-certification.

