## **ADVANTAGES**

Participants will receive a novel online program to reduce depressive symptoms free of charge, either immediately or after waiting for 6 months (i.e. all patients will receive treatment). Participants may also benefit from a thorough clinical and psychological examination conducted at V1 and V2 by authorized personnel under the supervision of experienced clinicians.

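### As written, the Safety Set and the mITT set hold no waitlist patients at week 12, so neither can give a contrast with the control arm

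*Supplement*

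**What the plan says.** SAP section 3.3 defines three sets. The full analysis set (FAS) takes every randomised patient with a post-baseline assessment. A second set is then added: "A modified ITT (mITT) population will be analysed in a sensitivity analysis". Its membership rule is "It includes those patients who have registered in the program MSDeprexis". The Safety Set follows the same rule, "All subjects who have registered in the program MSDeprexis will be included", and its patients are grouped as treated: "Subjects will be analysed according to the treatment they received". Neither registration rule says how waitlist patients are to be handled.

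Three other statements fix the timing:

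- SAP section 1, on the scope of the plan: "It describes the analysis after the first 12 weeks".
- SAP section 2.1, on the comparator: "the third group is a waitlist control group".
- Protocol section 7 (Advantages), on when participants receive the programme: "either immediately or after waiting for 6 months".

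On the planned outputs, SAP section 5.4 says "Adverse events will be summarized as frequencies and percentages by intervention group". SAP section 5.2 tests each active arm against WLC with a Dunnett test and analyses the SBQ-R in the same way as the primary endpoint.

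**The concern.** A waitlist patient has no programme to register in during the period this SAP covers. A set defined by registration therefore excludes the control arm by construction, whatever happens in the trial.

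For safety this matters because the harms the SAP names, new suicidality and worsening of depressive symptoms, also occur without treatment. In the phase II trial described in the protocol, worsening from below to above the clinical cut-off was seen in 3 waitlist patients and in no Deprexis patient. Without a control column, event rates in the active arms cannot be separated from natural course.

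For the mITT, a sensitivity analysis of the primary result must be able to estimate the primary contrasts, and both of those are against WLC. If the analyst adds the controls back informally, patients who engaged with the programme are compared with all controls. The SAP neither describes that choice nor warns of the selection it brings.

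**Working it through.** **1. Planned size.** Inputs from SAP section 2.3: 100 evaluable patients per arm, 20% dropout, standardised differences 0.5 and 0.8, Dunnett test at one-sided 2.5%.

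- Recruitment: 100 / (1 − 0.20) = 125 per arm; 3 × 125 = 375. This matches the plan.
- Power: the one-sided Dunnett critical value (two comparisons, correlation 0.5, 297 degrees of freedom) is 2.223. Simulated conjunctive power is 90.5% against the stated 90%. This also matches.

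The design is therefore a three-arm comparison in which WLC is a full group of 125.

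**2. Who qualifies at week 12.**

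| Arm | Planned | Can register by week 12? | Maximum in Safety Set or mITT |
|---|---|---|---|
| MSDeprexis | 125 | yes | 125 |
| MSDeprexisPlus | 125 | yes | 125 |
| WLC | 125 | no (access after 6 months) | 0 |
| Total | 375 | | 250 |

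The excluded share is 125 / 375 = 33.3%, and it is the entire control arm.

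**3. What can be computed in these sets.**

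- MSDeprexis vs WLC and MSDeprexisPlus vs WLC: undefined, since the control n is 0.
- An adverse event percentage for WLC: 0/0, undefined.
- MSDeprexis vs MSDeprexisPlus, the secondary comparison in SAP 5.2: still possible.
- The primary analysis: unaffected, because the FAS does not depend on registration.

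**4. Events concerned if the adverse event summary uses the Safety Set.** From Supplementary Table 1 (suicidality + worsening + other):

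- Control: 0 + 3 + 6 = 9
- iCBT: 0 + 1 + 5 = 6
- Guided iCBT: 0 + 0 + 3 = 3
- Total: 18. Control share: 9 / 18 = 50%. Worsening in Control: 3 of 3 + 1 + 0 = 4, or 75%.

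The table gives neither a time window nor denominators, and the protocol collects adverse events up to month 12. These shares apply to the week-12 analysis only on the assumption that the events fall within it.

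**5. Would counting later registration help?** The SAP puts no date on registration, so one could count waitlist patients who register after month 6. As an assumption, let 25%, 50% or 75% of 100 evaluable waitlist patients do so, with 100 in each active arm. Conjunctive power is then about 53%, 75% or 85%. The controls would also be selected by something that happens after the week-12 outcome, so the set would still not give a valid comparison.

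**The case against.** The best defence is that registration was meant only as a receipt-of-treatment condition for the active arms. Supplementary Table 1 supports this, since it has a Control column that the Safety Set as written could not produce. That is probably what the authors intended, but the SAP does not say it. For the mITT, the same reading makes the analysis runnable and leaves it open to an unacknowledged selection.

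A second defence also has force: no section assigns any analysis to the Safety Set. SAP 5.4 names no population. The SBQ-R analysis, run like the primary endpoint, may well use the FAS, and protocol sections 12.5.1 and 12.5.2 say that all analyses follow intention-to-treat. A reader might infer that control patients are removed from every safety analysis. The documents do not support that. The loss of the control column in the adverse event summary is an inference from the set's name and purpose, and the SBQ-R comparison with WLC may survive.

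Third, leaving out active-arm patients who never registered is in line with an exposure-based, as-treated safety set and is not a fault in itself.

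Finally, the mITT is only supportive. The confirmatory test, its error control and its power do not depend on it, and the LOCF and multiple imputation analyses are planned separately.

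**Conclusion.** The defect stands for contrasts with WLC. On the text, both registration-based sets have zero control patients at week 12 and at most 250 of 375 planned patients, so neither can estimate an effect or an excess of harm relative to control. This is a stated rule that gives the wrong set, rather than a detail left open.

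The conclusion assumes that registration is judged within the 12 weeks this SAP covers and that waitlist access follows the protocol. The figure of 250 uses planned numbers and full registration in the active arms.

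Two stronger readings should be avoided. It would be wrong to say that no between-arm comparison survives, because MSDeprexis vs MSDeprexisPlus remains possible in both sets. It would also be wrong to say that half of all events were in fact lost. The 9 of 18 is conditional on the Safety Set being used for adverse events and on the events lying within the window, and the published table does show Control.

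**What to change.** In SAP section 3.3, define the Safety Set as all randomised patients, with WLC patients as the untreated comparator until their first access to the programme. In sections 5.2 and 5.4, state which set each safety analysis uses: the Safety Set for adverse events, and either the Safety Set or the FAS for the SBQ-R.

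For the mITT, state that the registration condition applies to the two active arms only and that all WLC patients are kept. Label the result supportive, and note that conditioning on a post-randomisation behaviour in the active arms alone is open to selection bias.

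A complier-average estimate, with randomisation as instrument and registration as receipt, could be added but is not required. Its exclusion restriction would have to be stated. That restriction is doubtful for MSDeprexisPlus, where protocol section 5.1 has the therapist write weekly and offer help even to patients with no online activity, so assignment may act without programme use.

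The cost is a few sentences in the SAP. No new data are needed: the protocol's visit schedule records adverse events at weeks 4, 8 and 12 without restriction by arm, and Supplementary Table 1 shows that control events were recorded.

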## **4 Trial population**

### **4.1 Screening data**

Screening takes place within the participating centres. Available data on patients assessed for eligibility will be included within a CONSORT flow diagram.

### **4.2 Eligibility**

Patients need to be at least 18 years old with a neurologist-confirmed diagnosis of MS. They have self-reported depressive symptoms (BDI-Fastscreen  $\geq 4$ ) and are able to travel to the outpatient centre for two clinical assessments. Acute risk for suicide at baseline will lead to exclusion from the trial. For complete inclusion/exclusion criteria, see section 4 of the latest version of the study protocol.

### **4.3 Recruitment**

A CONSORT flow diagram will be calculated to show patient disposition including sample sizes for recruitment, randomization and analyses.

### **4.4 Withdrawal/follow-up**

Withdrawal rates will be calculated and reasons given within a CONSORT flow diagram.

### **4.5 Baseline patient characteristics**

Baseline characteristics and demographic data will be summarized descriptively stratified by treatment group:

- Age [years]
- Sex [female; male]
- Marital status [married or domestic partnership; separated or divorced; single, never married; widowed]
- Education [high school graduate, diploma or equivalent; associate degree, bachelor's degree; master's degree; doctoral degree]
- Employment status [unemployed or retired; homemaker; student, parttime; full time; other]
- Time since diagnosis
- Diagnosis subtype [primary progressive MS; secondary progressive MS; relapsing-remitting MS; unclear]
- Neurological status [Expanded Disability Status Scale (EDSS)]
- Level of disability [PDDS]
- Neurological function [BICAMS]

- Disease-modifying therapy.

## 5 Analysis

### 5.1 Outcome definitions

Depressive symptoms at baseline and at week 4, 8 and 12 (end of treatment) are measured with the BDI-II. BDI-II is a 21-question self-reported inventory for measuring the severity of depression. Each question has a set of at least four possible responses, ranging in intensity. To calculate the score a value of 0 to 3 is assigned for each answer. A higher total score indicates more severe depressive symptoms. The interpretation of these scores is:

- 0-13: minimal depression
- 14-19: mild depression
- 20-28: moderate depression
- 29-63: severe depression (2)

Quality of life is measured at baseline and at week 12 with the WHO-QoL BREF and with the MSIS-29. WHO-QoL BREF consists of 26 items, which are assigned to the four domains: physical health, psychological health, social relationships, and environment. Answers are on a 5-points Likert scale ranging from 1 (not at all) to 5 (completely). Items are scored from 1 to 5 and a score (0-100) is calculated using an algorithm (see Appendix 10 of (3)).

The Multiple Sclerosis Scale-29 includes two scales: physical impact (20 items) and psychological impact (nine items). All items have five response options from 1 (not at all) to 5 (extremely). A score (0-100) is calculated using the following algorithm: Physical scale items (1-20): sum, subtract 20, divide by 80, and multiply by 100, psychological scale items (21-29): sum, subtract nine, divide by 36, and multiply by 100 (4).

Fatigue is measured at baseline and at week 12 with the FSMC and the Chalder Fatigue Scale. FSMC is a 20-item scale with response option from 1 (Does not apply at all) to 5 (Applies completely). There are ten questions about the cognitive and ten questions about the motor fatigue, the total score can reach 100 points (extreme fatigue) (5).

The Chalder Fatigue Scale is an 11-item questionnaire with a 4-points Likert scale ranging from 0 (Less than usual) to 3 (Much more than usual). The sum of these items is the score, so it can range from 0 to 33 (6).

In addition, depressive symptoms are measured with the Mini-International Neuropsychiatric Interview (M.I.N.I.) and the MADRS. M.I.N.I. is a short structured diagnostic interview for the major Axis I psychiatric disorders in DSM-IV and ICD-10 (7).

MADRS is a ten-item questionnaire with a 7-points Likert scale from 0 to 6. The score is the sum of all items and ranges from 0 to 60 (8).

For safety analysis the SBQ-R is used to control suicidal ideation. The SBQ-R has 4 questions, where each question has an individual scale, and each response corresponds to a certain point value. The total score ranges from 3 to 18. The higher the score, the higher the likelihood of suicidal behavior (9).

To determine the neurological function the Symbol Digit Modalities Test (SDMT) is used. This test is part of the Brief Cognitive Assessment in MS (BICAMS). The SDMT consists of a row with nine symbols, where each symbol corresponds to a certain value. Below there are seven rows with 15 symbols each and the patient should assign the correct numerical value to as many symbols as possible within 90 seconds. The score is the number of correct assignments. There are two additional tests: The California Verbal Learning Test-II (CVLT-II T1-5). There is a 16-item list with words from four different topics, arranged randomly. The list is read aloud five times in the same order to the patient. Patients are required to recall as many items as possible, in any

order, after each reading of the list. The other one is the Brief Visuospatial Memory Test-revised (BVM-T-r). In this test 6 abstract figures are presented three times. In each of the three learning trials, the patient views the same array for 10 seconds. Then the array is removed and the patient is required to draw the stimulus array from memory, with the correct shapes in the correct position. Each design receives from 0 to 2 points representing accuracy and location, so the score ranges from 0 to 12 for each trial (10, 11).

To determine the neurological impairment the Patient Determined Disease Steps (PDDS) is used. There are 9 categories from 0 (no limitation of activities) to 8 (bedridden) describing the patients situation with a main focus on the ability to walk (12).

## 5.2 Analysis methods

### Primary endpoint

The primary outcome change in BDI from baseline to week 12 will be analysed by means of linear mixed effects models for repeated measures adjusted for baseline measurements with fixed effects for intervention, region (US, GER), time and baseline BDI score, and random subject effects for individual patients including all patients with at least one post-baseline measurement (13). Least squares means will be reported for the intervention groups with 95% CI as well as the difference between the least squares group means with 95% CI. MSDeprexis vs. WLC and MSDeprexisPlus vs. WLC will be tested by a Dunnett test controlling the familywise type I error rate at the level of 2.5% (one-sided). The primary hypothesis will be tested in a confirmatory manner:

$H_0^{(1)}: \mu_{WLC} \leq \mu_{Dep}$  vs.  $H_1^{(1)}: \mu_{WLC} > \mu_{Dep}$  and  $H_0^{(2)}: \mu_{WLC} \leq \mu_{DepPlus}$  vs.  $H_1^{(2)}: \mu_{WLC} > \mu_{DepPlus}$ , with  $\mu_{WLC}$ ,  $\mu_{Dep}$  and  $\mu_{DepPlus}$  being the means of the change in BDI from baseline to week 12.

In a secondary step, the added value of therapist email support MSDeprexis vs. MSDeprexisPlus at a two-sided level of 5%, if efficacy of MSDeprexis and MSDeprexisPlus for reducing depressive symptoms in MS could be demonstrated, will be determined.

SAS analysis:

```
proc mixed data =_data_t;
class group time region;
model score = group time group*time baseline baseline*time region / s ddfm=kr;
repeated time / subject=id type=un;
lsmeans group / adjust = dunnett;
```

In a sensitivity analyses last observation carried forward (LOCF) and multiple imputations (MI) will be used to deal with missing values for the BDI-II score (missing visits) and for each method an analysis of covariance (ANCOVA) for the BDI-II score after 12 weeks is carried out with BDI-II score at baseline as covariate.

In an exploratory analysis trends in the utilization time of MSDeprexis [number of days with activity within the program] in both intervention groups will be investigated.

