## 2.3 Sample Size

A sample size of 100 patients per intervention group gives a conjunctive power (probability of rejecting both null hypotheses comparing MSDeprexis and MSDeprexisPlus to waitlist control) of 90% for a Dunnett test at the usual one-sided significance level of 2.5% assuming standardized mean differences of 0.5 for MSDeprexis vs. WLC and 0.8 for MSDeprexisPlus vs. WLC in the primary outcome change in BDI from baseline to week 12. Adjusting for 20% dropout we aim to recruit 125 patients per group resulting in a total sample size of 375 patients. The power was simulated with 10,000 replications using EAST 6.3.

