# **3 Statistical Principles**

## **3.1 Confidence intervals and p-values**

If not specified otherwise, tests will be performed two-sided with a significance level of 5% and 95% confidence intervals (CI) will be provided for parameter estimates. For the primary analysis, MSDeprexis vs. WLC and MSDeprexisPlus vs. WLC will be tested by a Dunnett test controlling the familywise type I error rate at the level of 2.5% (one-sided).

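### The Dunnett adjustment is specified for the two primary tests but not for their 95% CIs, so a reported interval could exclude zero while the confirmatory test fails

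*Supplement*

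**What the plan says.** SAP 3.1 sets a general rule that applies unless something else is specified: "tests will be performed two-sided with a significance level of 5% and 95% confidence intervals (CI) will be provided for parameter estimates". Its only exception for the primary analysis concerns the test. The two comparisons with waitlist "will be tested by a Dunnett test controlling the familywise type I error rate at the level of 2.5% (one-sided").

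SAP 5.2 (Primary endpoint) has the same split. Least squares means are reported by group with 95% CIs, as is "the difference between the least squares group means with 95% CI". The sentence after that assigns the Dunnett procedure to the tests. The model code ends with "lsmeans group / adjust = dunnett"; it shows no confidence-limit option and so does not settle which interval is meant. Protocol 12.5.1 and 12.5.2 use equivalent wording.

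SAP 5.2 adds a third comparison, MSDeprexis versus MSDeprexisPlus, at a two-sided 5% level, conditional on efficacy having been shown for both versions.

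**The concern.** The plan names a multiplicity adjustment for the test and none for the interval printed beside it. If the interval is ordinary, the two use different critical values. A difference that falls between them would be reported with a CI on the favourable side of zero and a non-significant confirmatory test.

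Many readers judge efficacy from the estimate and its interval, so the headline result could appear to contradict its own pre-specified conclusion. Two features of SAP 5.2 add to this. The guided-versus-unguided comparison opens only after both primary tests succeed, and a contradictory interval would blur whether that condition was met. The continuous secondary endpoints follow a similar approach and inherit the ambiguity. A choice left open in the SAP could also be made after the results are known.

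**Working it through.** **Inputs**
- Familywise level: one-sided 2.5%, Dunnett, two comparisons with waitlist (SAP 3.1, 5.2).
- Planning effects (SAP 2.3): "assuming standardized mean differences of 0.5 for MSDeprexis vs. WLC and 0.8 for MSDeprexisPlus vs. WLC".
- Evaluable patients: 100 per arm, inflated to 125 for 20% dropout (SAP 2.3).
- Allocation 1:1:1 (SAP 2.2), which gives a correlation of 0.5 between the two test statistics.
- Assumed here: equal variances and a pooled t form with 3 × 100 − 3 = 297 degrees of freedom. The mixed model's degrees of freedom will differ slightly.

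**Step 1: reproduce the plan's own figure.** A simulation of the single-step Dunnett test (1,000,000 replications, 100 per arm) gives a critical value of 2.218 and a conjunctive power of 90.6%, against the stated 90%. A step-down Dunnett test and an unadjusted analysis both give 94.1%. The stated power therefore fits the single-step test, which has a matching simultaneous interval. The recruitment figures are also exact: 100/(1 − 0.2) = 125, and 3 × 125 = 375.

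**Step 2: the two critical values.** An ordinary 95% CI excludes zero when |t| > 1.968 (297 df). The Dunnett test needs t > 2.218. The width ratio is 2.218/1.968 = 1.127, about 13%.

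**Step 3: the conflict band.** In SD units the standard error of a difference is √(2/100) = 0.1414.
- Lower edge: 1.968 × 0.1414 = 0.278 SD.
- Upper edge: 2.218 × 0.1414 = 0.314 SD.

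An observed difference between these has an ordinary CI that excludes zero and a Dunnett test that fails. With 125 evaluable per arm the band is 0.249 to 0.281 SD.

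**Step 4: how often this happens.** For a true standardized difference δ, the mean of t is about δ√50, and the chance of conflict for one comparison is Φ(2.218 − δ√50) − Φ(1.968 − δ√50).

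| δ | δ√50 | Chance of conflict |
|---|---|---|
| 0.80 (MSDeprexisPlus, planned) | 5.657 | 0.02% |
| 0.50 (MSDeprexis, planned) | 3.536 | 0.0938 − 0.0585 = 3.5% |
| 0.46 | 3.253 | 5.1% |
| 0.40 | 2.828 | 7.6% |
| 0.36 | 2.546 | 9.0% |

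The values below 0.50 come from Protocol 2.1. It cites a standardized difference of 0.46 in size for CBT in MS, d = 0.36 and d = 0.46 in earlier Deprexis trials, and a pooled g of 0.54 with a 95% CI from 0.39 to 0.69. With 125 evaluable per arm the figure for MSDeprexis at δ = 0.50 falls to about 1.8%.

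**Step 5: joint behaviour** (bivariate normal, correlation 0.5). Two ordinary 95% intervals jointly cover both true differences with probability about 91%. Under the global null, at least one excludes zero in the favourable direction with probability about 4.5%, against the 2.5% that the test controls. The chance of at least one conflict under the global null is about 2.2%.

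**The case against.** The strongest reply is that the SAP never calls these intervals unadjusted. A reader might infer that it prescribes them, but it does not. That reading comes from applying the default in 3.1 where no exception for intervals is given, and the code requests neither kind. This part of the objection stands, and the point is worded accordingly.

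A reader might also infer that the trial runs at a familywise error of 4.5%. The documents do not support that. SAP 3.1 and 5.2 place the confirmatory decision on the Dunnett test, and nothing lets an interval establish efficacy or open the later comparison. The 4.5% arises only if someone substitutes the intervals for the test. Nor does the SAP promise joint coverage, so 91% describes what ordinary intervals would deliver and is not a broken commitment.

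It is also fair to say that adjusted p-values beside marginal intervals are an acceptable reporting choice when labelled, and that the sentence on differences covers the guided-versus-unguided contrast too, for which an ordinary 95% CI matches its two-sided 5% test. Both remarks narrow the point without removing it. The SAP contains no such label, and for the two confirmatory differences the default interval does not match the test.

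**Conclusion.** The point holds as a matter of reporting consistency. Under the SAP's own default, the two primary differences would carry ordinary 95% CIs beside a test with a stricter threshold. The two disagree for observed differences of about 0.278 to 0.314 SD with 100 per arm. The chance of this is small at the planning effects (about 3.5% for MSDeprexis, 0.02% for MSDeprexisPlus). It is about 5 to 9% for MSDeprexis if the true effect is 0.46 to 0.36, values found in the protocol's own background evidence.

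The confirmatory conclusion, its type I error, the power and the sample size are all unaffected. The figures rest on equal variances, 100 evaluable patients per arm and the pooled t form; more evaluable patients lower the conflict chance at the planning effects. This is a minor but cheap clarification, best made before the results are known.

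**What to change.** State in SAP 3.1 and 5.2 that the two week-12 differences versus waitlist are reported with Dunnett-adjusted simultaneous 95% CIs, and that any ordinary interval for them is descriptive. Keep the ordinary 95% CI for MSDeprexis versus MSDeprexisPlus.

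The two-sided simultaneous critical value with 100 per arm is 2.221, against 2.218 for the one-sided test, so interval and test then agree for practical purposes.

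Adding a confidence-limit option to the line shown is not enough. The model contains a group-by-time term, and `lsmeans group` alone averages over the modelled time points, so it is not a week-12 contrast. The code should form the two week-12 group contrasts and request adjusted confidence limits for them.

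Cost: one sentence in each of the two sections, a small change to the contrast code, and primary intervals about 13% wider (half-width 0.314 instead of 0.278 SD with 100 per arm).

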### 1.3 Primary objective and endpoint

To determine if MSDeprexis is effective for reducing **depressive symptoms** at the end of treatment (week 12), the Beck Depression Inventory – II (BDI-II)) in patients with MS is used and compared to the control group. Because the literature strongly suggests that therapist-guided internet-based interventions lead to better outcome MSDeprexis with an added email support (MSDeprexisPlus) is also compared to the control group after 12 weeks (MSDeprexis vs. WLC and MSDeprexisPlus vs. WLC).

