### 12.5.1 Hypotheses

**Primary hypothesis:** All analyses will be conducted as intention-to-treat (ITT). To definitively test the effectiveness of Deprexis for reducing depressive symptoms in MS at the end of treatment, the primary outcome change in BDI from baseline to week 12 will be analyzed by means of linear mixed effect models for repeated measures adjusted for baseline measurements with fixed effects for intervention, center, time and baseline BDI score, and random subject effects for individual patients including all patients with at least one post-baseline measurement (29). Least squares means will be reported for the intervention groups with 95% confidence interval (CI) as well as the difference between the least squares group means with 95% CI. Deprexis vs. WLC and DeprexisPlus vs. WLC will be tested by a Dunnett test controlling the familywise type I error rate at the level of 2.5%

(one-sided). *The primary hypothesis will be tested in a confirmatory manner.* In a secondary step, we will determine the added value of therapist email support Deprexis vs. DeprexisPlus at a two-sided level of 5%, if efficacy of Deprexis and DeprexisPlus for reducing depressive symptoms in MS could be demonstrated.

**Secondary hypotheses:** The analyses of secondary and tertiary endpoints (such as BDI-FS, QoL, cognitive function and fatigue scales) will follow the same approach as the analyses described for the primary endpoint. The proposed trial will create a large data set from n=400 MS patients and followed for 12 months that will enable us to gain valuable insight into the potential predictors, confounders, intermediates in the causal pathway, and interactions of Deprexis(Plus) treatment effects. In supporting exploratory analyses we will investigate potential moderators of treatment effects by including these and their interaction with treatment in the linear mixed effects models described above. Potential moderators include disease-modifying therapies (DMTs), level of disability at baseline (as measured by Disease Steps and patient-rated EDSS), cognitive status at baseline (as measured by BICAMS), and level of fatigue at baseline (as measured by the FSMC).

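### The printed primary SAS code compares arms on the average of weeks 4, 8 and 12, while the confirmatory hypotheses concern the change to week 12

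*Supplement*

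**What the plan says.** The stated target is consistent. SAP 1.3 places the primary objective "at the end of treatment (week 12), the Beck Depression Inventory" being the instrument. The confirmatory nulls in SAP 5.2 are written on arm means defined as "being the means of the change in BDI from baseline to week 12". SAP 2.3 assumes its standardized differences of 0.5 and 0.8 for that same change.

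The model uses more visits than week 12: "Depressive symptoms at baseline and at week 4, 8 and 12 (end of treatment) are measured with the BDI-II". The printed code treats time as a class factor with an unstructured covariance and fits "model score = group time group*time baseline baseline*time region / s ddfm=kr". Its only comparison statement is "lsmeans group / adjust = dunnett".

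The SAP's model text lists "fixed effects for intervention, region (US, GER), time and baseline BDI score, and random subject effects for individual patients". It contains no group-by-time interaction and does not say at which visit the least squares means are taken. Protocol 12.5.1 has the same structure, with centre in place of region: "fixed effects for intervention, center, time and baseline BDI score".

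**The concern.** When group*time is in the model, the LS-means for group are group means averaged with equal weight over the levels of time. The Dunnett comparisons then contrast a 12-week average, and nothing in the code isolates week 12. The two targets agree only if the treatment effect is the same at weeks 4, 8 and 12. The interaction term is in the model because that is not assumed. A changing effect is also plausible here: the program is a sequence of 10 modules plus an introduction and a summary, used over 12 weeks, so many patients may have met only part of it by week 4.

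The confirmatory p-values and the headline differences with their confidence intervals are at stake. So is the step to MSDeprexis versus MSDeprexisPlus, which is tested only if both primary comparisons succeed. An effect that builds up would be understated. An early effect that fades could be reported as efficacy at the end of treatment.

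**Working it through.** **Inputs from the documents.** 100 patients per arm; standardized differences of 0.5 and 0.8 at week 12; Dunnett test at one-sided 2.5%; 90% conjunctive power; 20% dropout (SAP 2.3). Post-baseline BDI-II at weeks 4, 8 and 12 (SAP 5.1).

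**Assumptions, because the documents give no figures.** Equal SDs at the visits; compound-symmetric correlation ρ of 0.5 to 0.8 between visits; the effect profiles below; complete data for 100 per arm; weeks 4, 8 and 12 as the levels of time, since baseline enters as a covariate. The content of the analysis dataset is not defined. If a baseline row were kept as a time level, the average would lie further from week 12.

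**1. The plan's own figure.** Single-step Dunnett, two comparisons sharing a control (correlation 0.5), 3 × 100 − 3 = 297 degrees of freedom: critical value 2.22. Simulated conjunctive power at 0.5 and 0.8 is about 90.5%, which reproduces the stated 90%. Dropout: 100 / 0.8 = 125 per arm, 375 in total, as stated. The sample size therefore belongs to a week-12 contrast.

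**2. What the code estimates.** The SAP's fixed effects were fitted to 3,000 simulated patients, with true differences rising linearly to −5.0 and −8.0 at week 12. The true three-visit averages are then −5.0 × (1/3 + 2/3 + 1)/3 = −3.33 and −8.0 × 2/3 = −5.33.

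| Contrast against control | MSDeprexis | MSDeprexisPlus |
|---|---|---|
| Group LS-means (as printed) | −3.35 | −5.30 |
| Group*time LS-means at week 12 | −5.06 | −7.98 |

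The printed statement recovers the average, not the week-12 difference.

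**3. Power of the averaged contrast.** Let m be the mean of the profile as a fraction of the week-12 effect. The SD of a three-visit mean is SD × √((1 + 2ρ)/3), which is 0.816 SD at ρ = 0.5 and 0.931 SD at ρ = 0.8. The effective standardized differences are 0.5m and 0.8m divided by that factor. For a linear build-up, m = 0.667: at ρ = 0.5 they are 0.333/0.816 = 0.41 and 0.533/0.816 = 0.65; at ρ = 0.8 they are 0.36 and 0.57.

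| Effect at weeks 4 / 8 / 12 (% of week-12 effect) | m | Conjunctive power, ρ = 0.8 to 0.5 |
|---|---|---|
| 33 / 67 / 100 | 0.667 | 62% to 74% |
| 80 / 90 / 100 | 0.90 | 88% to 95% |
| 100 / 100 / 100 | 1.00 | 94% to 98% |
| Week-12 contrast, any of these profiles | – | about 90.5% |

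**4. Error rate for the stated hypotheses.** Take effects of 0.5 and 0.8 at week 4, half of that at week 8 and none at week 12. Both week-12 nulls are then true. The averaged effects are (0.5 + 0.25 + 0)/3 = 0.25 and (0.8 + 0.4 + 0)/3 = 0.40. The averaged test rejects at least one null in about 82% (ρ = 0.8) to 91% (ρ = 0.5) of trials, against an intended familywise level of 2.5%.

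**The case against.** The best defence is that the endpoint is right everywhere it is defined. The objective, the sample size, the outcome sentence and both hypotheses name week 12, and a careful programmer could treat the code as a sketch. That stands to this extent: the fault is a contradiction between code and hypotheses inside SAP 5.2, and the harm follows only if the code is run as printed. It does not remove the point, because the model text gives no visit and no interaction from which the programmer could recover the week-12 contrast.

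It is also true that the LOCF and multiple-imputation ANCOVAs use the BDI-II score after 12 weeks, so they could expose an early effect that has gone. They are sensitivity analyses and do not replace the confirmatory test.

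A reader might infer more than the documents support:

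- **That power is necessarily lost.** It can be higher or lower. With a constant effect the averaged test is the more powerful one.
- **That the code uses the wrong control arm.** The default control depends on how group is coded, and the coding is not given. The text names WLC as comparator for both tests.
- **That a two-sided default changes the decision.** The simulated one-sided 2.5% and two-sided 5% Dunnett critical values are both 2.22, so a result in the favourable direction is judged the same way.
- **That SAP text and code disagree on centre versus region.** Both use region. Only the protocol says centre, and it leaves analysis details to the SAP.
- **That the covariance wording drives the problem.** A random subject effect in the text and an unstructured matrix in the code should be worded alike, but an unstructured matrix includes the pattern that a random intercept induces.

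**Conclusion.** The point holds. As printed, the confirmatory comparison tests an equal-weight average over weeks 4, 8 and 12, while the nulls concern week 12. That mismatch follows from the code and needs no assumption about the data beyond the three post-baseline visits entering as levels of time.

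Its numerical effect does rest on assumptions, namely the effect profile and visit correlations of 0.5 to 0.8. Within them, conjunctive power ranges from 62% to 98% against about 90.5% for the intended contrast, and an effect that has vanished by week 12 gives a rejection in about 82-91% of trials. It should be corrected before the analysis is run, because it decides the primary p-values and estimates. It is not evidence of a wrong endpoint or of a wrong sample size.

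**What to change.** Add the group-by-time interaction to the model text, together with the baseline-by-time term already in the code, and keep the SAP's region term. Take the two primary contrasts, MSDeprexis minus WLC and MSDeprexisPlus minus WLC, from group*time at week 12 (for example with an LSMESTIMATE statement), and apply the multiplicity adjustment to those two contrasts. Name WLC as control and state the one-sided direction in the code, for clarity. Say in the text that the reported least squares means and differences are those at week 12. Report the time-averaged effect as supportive.

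This costs a few lines of text and code, with no new data and no change in sample size. The one downside is that the week-12 contrast is somewhat less precise than the average if the effect is constant over time (about 90.5% against 94-98% conjunctive power under the assumptions above). It is, however, the quantity on which the trial was sized.
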